### Statistical analyses

We compute descriptive statistics to describe the characteristics of the target population and general practices and to investigate comparability of study groups at baseline. Relevant statistical tests (e.g., t-test, chi-square, analysis of variance, regression analysis) will be applied to analyse effects on primary and secondary outcome measures (level of significance is 0.05; two-tailed). Data will be analysed according to the intention-to-treat principle. In all analyses, there will be a correction for possible baseline differences between participants or general practices. In addition, we will perform sub-group analyses to investigate whether certain groups of older people benefit more from the [G]OLD-protocol than other groups. We will use the software package SPSS for Windows, version 17.0, for all statistical analyses.

Data gathered as part of the process evaluation will be analysed using descriptive techniques, such as calculating scores (e.g., number of drop-outs), narrative description of procedures, and identifying themes in the interviews.

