### Selection of general practices

General practices (n = 21) who visited older people at home as part of our pilot study [30] were excluded from participation to prevent contamination of prior experience. We approached 188 general practices in the three regions for participation in this study. Practices in Midden-Limburg were only invited to participate in the control group, since insufficient general practices from the other two regions were willing to participate in the control group. GPs who indicated to be actively engaged in or are planning to start with the identification and follow-up of frail older people in a systematic way were ineligible to participate (n = 12 practices). The availability of a practice nurse who has time for care for older people is a prerequisite for intervention practices. Practice nurses work in general practices, and provide screening, treatment, care and education mainly to patients with chronic diseases and older people.

Reasons of general practices for non-participation were: no time (e.g., due to other priorities, staff changes or participation in other research projects) (35.0%), no interest to participate in the present study (31.7%), interested in [G]OLD-intervention but not in research (19.5%), or no reason was mentioned (13.8%).

Fourteen general practices agreed to participate as intervention practice and 13 general practices consented to participate in the control group. Control practices were matched to intervention practices based on the presence of primary care professionals within general practices to ensure comparability at baseline. We assume that close proximity of various primary care disciplines facilitates collaboration in organising and/or delivering appropriate care to older people [31]. After the recruitment phase, one intervention practice and two control practices dropped out due to a lack of time to select older people eligible for participation. As a result, 24 general practices were included in this study.

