### Sample size considerations

The sample size calculation is based on the primary outcome measure health-related quality of life (subscale ‘general health perception’) as measured by the RAND-36 [35,36]. We aim to demonstrate a clinically relevant difference between the mean change score of the intervention and control group of 5.0 on the transformed subscale. This implies a standardised effect size of 0.24 (given SD = 21.2). Based on this and applying a significance level (α) of 0.05 and a power of 0.90, the minimally required number of participants is 564 (n = 282 per study group) using an independent samples t-test (two-sided). However, calculations that take into account the interdependency of the measurements within a cluster (i.e., general practice) and correct for the cluster effect result in a required sample size of 1,200 older people (n = 600 per study group).

We expected a response rate of 50% on the information letter and consent form sent to eligible older people for participation and a drop-out rate of 30%. Accounting for drop-out, we planned to enrol 858 older people per study group to have a sufficient number of participants per group (600 older people) at the end of 18 months follow-up (see also Figure 1). Because of the expected response rate of 50%, we planned to approach at least 1,716 community-dwelling older people per study group for participation.

Since the amount of home visits that is performed depends on the PNs available time, we expected a variation in cluster sizes. This is compensated for by sampling 25% more clusters (i.e., general practices) [42].

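### The trial is sized for clustering by practice, but the tests named for the effect analysis do not account for it in ordinary form; run at patient level, a nominal 5% test would have about 12% to 18% type I error

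*Protocol article*

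**What the plan says.** In the protocol article, the Abstract gives 13 intervention and 11 control practices. Each practice joined one arm as a whole, so the practice is the unit of allocation. Under Selection of general practices, the arms were made comparable at practice level: "Control practices were matched to intervention practices based on the presence of primary care professionals within general practices".

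Sample size considerations treats the practice as a cluster. An independent-patient calculation gives 282 per group. The section then says that calculations which "take into account the interdependency of the measurements within a cluster (i.e., general practice" raise this to 600 per group, and it adds 25% more practices because cluster sizes will vary.

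Statistical analyses, the next section, states how effects will be tested: "Relevant statistical tests (e.g., t-test, chi-square, analysis of variance, regression analysis) will be applied to analyse effects on primary and secondary outcome measures", with "level of significance is 0.05; two-tailed". Practices are mentioned once more in the plan for the effects, as something whose baseline imbalance will be adjusted for in all analyses. The section names no multilevel model, GEE, cluster-robust standard error or practice-level analysis.

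**The concern.** The two sections do not fit together. The first accepts that patients in one practice carry overlapping information and more than doubles the sample for it. The second offers, as its examples for the primary and secondary outcomes, methods that in everyday use count each patient as independent.

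The baseline adjustment does not close the gap. It shifts the estimated group means for measured imbalances and may absorb some between-practice variance. It does not put the remaining within-practice correlation into the standard error.

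At stake is the meaning of the stated significance level. Standard errors that are too small give confidence intervals that are too narrow and too many false-positive findings. The study is also non-randomised, so false precision would add to a confounding risk that it already carries.

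**Working it through.** **Inputs.** From Sample size considerations:
- difference: "mean change score of the intervention and control group of 5.0 on the transformed subscale"
- spread: "This implies a standardised effect size of 0.24 (given SD = 21.2"
- error rates: "applying a significance level (α) of 0.05 and a power of 0.90"
- test: "using an independent samples t-test (two-sided"
- 282 per group before and 600 per group after the cluster correction

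The article gives no intracluster correlation (ICC), assumed cluster size or design effect, so the design effect has to be derived.

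**Step 1: reproduce the 282.** n per group = 2 × (z_0.975 + z_power)² × (SD/difference)², with (21.2/5)² = 17.98.
- Power 0.90: 2 × (1.960 + 1.282)² × 17.98 = 378 (365 with the effect size rounded to 0.24).
- Power 0.80: 2 × (1.960 + 0.842)² × 17.98 = 283 after rounding up.

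The stated 282 therefore matches 80% power, not the stated 90%. One-sided versions give 223, 259 and 308 at 80%, 85% and 90% power, and none matches. The later steps do reproduce: 600/0.70 = 858 after rounding up, and 858/0.50 = 1,716.

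**Step 2: implied design effect.** DE = n after / n before. Because of step 1 there are two candidates for the figure that was scaled up to 600:
- from 282: DE = 600/282 = 2.13
- from 378: DE = 600/378 = 1.59

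With an assumed 50 patients per practice, ICC = (DE − 1)/49, which is about 0.023 and 0.012. With 600/11 = 55 or 600/13 = 46 patients per practice, the ranges are 0.021 to 0.025 and 0.011 to 0.013.

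**Step 3: effect of ignoring practice.** The unadjusted standard error is 1/√DE of the true one. The actual type I error is 2 × [1 − Φ(1.96/√DE)].

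| Base for the 600 | DE | Standard error too small by | Actual type I error | Multiple of 0.05 |
|---|---|---|---|---|
| 282 (stated) | 2.13 | 31% | 0.179 | 3.6 |
| 378 (90% power) | 1.59 | 21% | 0.120 | 2.4 |

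Coverage of a nominal 95% interval would be about 1 − 0.179 = 82% or 1 − 0.120 = 88%.

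**Step 4: check by simulation.** With 13 and 11 practices of 46 and 55 patients and 100,000 runs, the patient-level t-test rejected a true null hypothesis in 0.181 of runs (DE 2.13) and 0.122 (DE 1.59). A t-test on practice means in the same data gave 0.049 in both cases.

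**Step 5: the 25% allowance.** As written, this is an addition in practices, separate from the 600. If the 600 already contained it and it is stripped out (600/1.25 = 480), DE is 480/282 = 1.70 with type I error 0.133, or 480/378 = 1.27 with 0.082. The last figure lies below the 12% to 18% range but still above 5%. It is a low figure, because unequal practice sizes themselves increase the variance of an unadjusted comparison.

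**The case against.** The strongest reply is that the methods are given as examples. Regression analysis can mean multilevel regression, analysis of variance can carry practice as a random factor, and a t-test on practice means is a valid cluster analysis. The section nowhere says that clustering will be ignored. The document is a journal article, and a full analysis plan, not shown here, may specify the model.

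Much of this stands. A reader might infer that the plan is committed to independent-patient tests, or that its two sections flatly contradict each other. The text supports neither, so the inflation is conditional on running the tests in ordinary patient-level form. What does not stand is the defence that this is only omitted detail. The article does name methods for the effects, and it does say how practices enter every analysis. Neither statement carries the clustering that the preceding section treats as essential.

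A second reply is that the design effect is not the plan's own figure. That is correct, and it is why the size is given as a range. A reader might infer from 600/282 that type I error would more than triple. Tripling needs a design effect of at least 1.85, and the 282 on which 2.13 rests does not match the stated power.

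A third is that the ratio comes from one RAND-36 subscale. That also stands: nothing in the article supports applying the same factor to disability (GARS), health care use, admissions or mortality.

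**Conclusion.** The point holds in conditional form. The sample size accounts for clustering by practice. The methods named for the effects do not do so in their ordinary form, and baseline adjustment does not supply what is missing. If they are run at patient level, the stated 5% two-sided test on RAND-36 general health perception would have a type I error of about 12% to 18%.

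The range assumes that the cluster correction took either 378 or 282 to 600, that the resulting design effect reflects the true correlation, and that adjustment for practice characteristics removes none of it. Even the lower end more than doubles the nominal rate. For the other outcomes the direction is the same wherever they correlate within practices, but the size cannot be derived from the article. The matter bears on the primary inference and should be settled before the effects are analysed.

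**What to change.** In Statistical analyses, replace the listed tests for effect estimation with an analysis that accounts for practice:
- **Questionnaire outcomes:** for example, a linear mixed model with a random intercept for practice, repeated measures within patient over the four time points, and small-sample degrees of freedom (such as Satterthwaite) for 24 practices. The mix of primary care professionals on which practices were matched is a natural practice-level covariate.
- **Binary and count outcomes:** a cluster-adjusted equivalent with a small-sample correction.
- **Baseline description:** ordinary t-tests and chi-square tests can stay.

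Other valid choices, such as a practice-level analysis or GEE with a small-sample correction, would serve equally well. What matters is that one is named. Stating the ICC and cluster size behind the 600, and reconciling the 282 with the stated power, would let a reader replace the range above with a single figure.

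The cost is a change of wording, slightly more analysis work and wider confidence intervals. No new patients or data are needed. The change corrects the standard errors only. Allocation was not random, and practices in one region (Midden-Limburg) were invited only as controls, so confounding remains whichever model is used.

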## Discussion

In the present paper, the design of a longitudinal, quasi-experimental study is presented to investigate the effects of the early detection of health problems among community-dwelling older people and their subsequent follow-up within the chain of care by general practices. In contrast to existing studies, we purposefully chose for a quasi-experimental design. Although randomised controlled trials are widely accepted as the “gold standard” for evaluating the effectiveness of interventions, they create artificial situations that may hinder the translation of research findings into practice [43-45]. Moreover, the study may suffer from the uncertain commitment of the people delivering the intervention (in this case the general practice’s staff) to the changes to be made. Routinisation of working methods in daily practice must take place to ensure sustainability of the [G]OLD-protocol [46], which is more difficult to realise within a randomised design. Our combination of an effect study and a thorough process evaluation should provide sufficient information with respect to the feasibility and external validity of the [G]OLD-protocol within general practices.

Furthermore, we predominantly used the Chronic Care Model for redesigning primary care practice as applying elements of this framework appears to lead to improved patient care and better health outcomes among patients [17]. We additionally expect that the multidimensional [G]OLD-instrument will be of added value in providing a comprehensive overview of the older person’s health status, compared to intervention programs that only focus on a limited number of tests or questions in only one or two domains.

Challenges faced during the intervention period are managing internal and external factors (e.g., changes in the general practice’s policy or reimbursement of medical expenses by insurance companies) to allow for continued and adequate implementation. Furthermore, considering the current interest of general practices in care for older people, general practices who participate in the control group are closely monitored until the end of the follow-up period to find out if they implement any activities that are similar to practices applying the [G]OLD-protocol. They may undertake initiatives that improve their care for older people and this may distort the intervention effect. Also, several factors may influence the extent to which general practices are successfully redesigned, such as the influence of existing routines and the care providers own clinical opinion (or “gut feelings”) on medical decision-making and referring older patients to adequate care and/or well-being facilities. Although we provided the necessary guidelines and recommendations to facilitate this process, GPs and practice nurses may not have ignored their own medical expertise in deciding about the diagnosis of health problems and/or referral and follow-up. The process evaluation will provide insight in the extent to which general practices redesign their care delivery to older people according to the [G]OLD-protocol. Results of the effect and process evaluation will become available in 2013.

## Abbreviations

ADL: Activities of Daily Living; BMI: Body Mass Index; CCM: Chronic Care Model; GARS: Groningen Activity Restriction Scale; [G]OLD: Getting OLD the healthy way; GP: General Practitioner; IADL: Instrumental Activities of Daily Living; n: Sample size; PGC Morale Scale: Philadelphia Geriatric Center Morale Scale; RAND-36: Research and Development-36; SD: Standard Deviation.
